### Data Collection and Management

Data will be collected by dedicated staff at the study center, and both the electronic medical record and CRF will be used to collect the data. In principle, missing values are not allowed in the report form. Particularly, important measures (the primary safety measure) must be clearly reported. If a test result is zero or if measurement fails, corresponding symbols (eg, “0” for zero values and “NM” for “not measured”) will be used instead of leaving the field vacant. This ensures a clear distinction from missing values. If there are missing values, the original data should be searched first to determine whether the data are missing. If it is indeed missing, the data should be filled in. If the missing value is an important indicator related to safety, the participant should be informed to review it immediately to ensure their safety. If the missing values affect the outcome, the case will be excluded.

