#### Randomization and Blinding

##### Randomization

The randomization sequence will be computer-generated by an independent statistician using SPSS Statistics (version 23.0; IBM Corp), using a block randomization method with a 1:1 allocation ratio. Sequentially numbered, opaque, sealed envelopes will be used to implement allocation concealment. Each envelope will contain a card specifying the random number, sequence number, and group assignment. After obtaining written informed consent, eligible participants will be assigned to either the treatment group or the control group by opening the next consecutively numbered envelope, and it is ensured that the random allocation sequence remains unknown to the researchers before enrollment to prevent selection bias.

##### 
Blinding

Due to the specific nature of the shallow needling procedure, we could not blind the investigators and participants, but outcome assessors and statisticians would be unaware of the trial-group assignments.

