### Outcome Measures

#### Primary Outcome Measures

PSQI [29] is a questionnaire used to assess an individual’s sleep quality, with good reliability and validity, indicated by a Cronbach α coefficient of 0.83 and a test-retest reliability of 0.85 [30]. It consists of 7 components: subjective sleep quality, sleep latency, sleep duration, habitual sleep efficiency, sleep disturbances, use of sleeping medication, and daytime dysfunction. The total score ranges from 0 to 21. A global PSQI score greater than 7 indicates the presence of sleep disorders, with higher scores reflecting poorer sleep quality. PSQI will be assessed before treatment, after treatment, and 4 weeks after treatment completion (follow-up).

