### Statistical Analysis

In this study, data will be analyzed with SPSS (version 23.0) software. Continuous variables will be reported as means and SDs, and categorical variables will be presented as frequencies or percentages. To compare continuous variables between the 2 groups, normality and homogeneity of variance will be initially evaluated. If these assumptions are satisfied, a 2-tailed *t* test will be used. Otherwise, a nonparametric rank-sum test will be used. Categorical variables will be analyzed using the chi-square test or Fisher exact test. *P* values of .05 or less will be considered statistically significant.

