### Quality Control

All participants, including acupuncturists, evaluators, and statisticians, will be required to undergo training to ensure the quality of the studies. By formulating detailed and operable clinical trial specifications, the intervention will be based on careful adherence to the standard operating procedures.

All participants, including acupuncturists, evaluators, and statisticians, need to be trained to ensure the consistency of relevant data collection and the quality of research through the development of detailed and operational clinical trial protocols. The intervention will be based on careful adherence to standard operating procedures, and the acupuncturists will perform standardized shallow needling procedures according to the standard acupoint positioning. After the training, the assessment effects of the scale by outcome evaluators need to be checked for consistency, mainly including the same case being scored by independent examination by several outcome evaluators and the same case being scored multiple times by one evaluator to ensure consistency of the scores.

The investigator will fill in all cases truthfully and carefully according to the design requirements of the CRF. Study medical records and CRFs are original records and cannot be altered.

Laboratory data in clinical trials should be documented, and the original report or photocopy needs to be glued to the CRF.

In order to effectively improve the compliance of the participants, during the case screening and enrollment stage, it is necessary to maintain a patient and careful attitude; fully explain the purpose, process, and significance of the study to the participants; and ensure that the participants clearly understand the relevant content. At the same time, the participants will be clearly informed to strictly follow the established requirements to ensure the smooth progress of the study and the accuracy of the data.

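### The missing-data rule lets randomised participants be excluded on post-randomisation data, in undefined terms, which can bias the PSQI comparison in either direction

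*Protocol article*

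**What the plan says.** The rule is in the protocol article, Data Collection and Management. Staff first check the source data to see whether a value is really absent. Then: "If it is indeed missing, the data should be filled in". No method or source for completing it is given. After a sentence on safety values, the paragraph ends: "If the missing values affect the outcome, the case will be excluded". It does not say what it means for a missing value to affect the outcome, who decides, or when.

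Other sections bear on this:
- **Primary Outcome Measures:** PSQI (0 to 21) is measured before treatment, after treatment and 4 weeks after treatment ends, so each participant should have one baseline and two post-baseline scores.
- **Statistical Analysis:** a two-group t test, or a rank-sum test if its assumptions fail. No analysis population, imputation method or sensitivity analysis is named here or elsewhere.
- **Randomization and Blinding:** of the procedure's nature, the authors write "we could not blind the investigators and participants". Outcome assessors and statisticians are blinded.
- **Interventions:** both arms take eszopiclone; only the treatment arm also attends needling, 5 times a week for 4 weeks.
- **Sample Size:** 10% dropout is allowed for, with 62 participants per group.

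**The concern.** Randomisation protects the comparison only as long as the groups analysed are the groups randomised. This rule makes membership of the analysed set depend on what happens afterwards. A participant with a missing post-treatment PSQI is the plainest case it would remove.

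Removal does no harm if those removed resemble those kept, or if the distortion is the same in both arms. Neither can be taken for granted here. Participants know their treatment, and the arms carry different attendance burdens (5 × 4 = 20 needling sessions against none). If poor responders leave the needling arm, the benefit is exaggerated; if they leave the control arm, it is hidden. Recruiting 62 instead of 56 per group protects precision against loss but does nothing about bias.

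The two instructions also leave staff without a usable boundary. Once a value is confirmed absent from the source, nothing says what it may be completed from, or when completion gives way to exclusion.

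**Working it through.** **1. The plan's own figures.** Inputs from Sample Size: 79.48% against 98%, α 0.05 (taken as two-sided), power 0.90, 1:1.

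n = (1.960 + 1.282)² × [0.7948 × 0.2052 + 0.98 × 0.02] / (0.98 − 0.7948)² = 10.51 × 0.1827 / 0.0343 ≈ 56 per group, as stated.

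For dropout, 56 × 1.10 gives 62 and 56 / 0.90 gives 63; the stated figure is 62. Expected loss is 62 × 0.10, about 6 per group.

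**2. Direction.** Let m be the share excluded in an arm and g the mean PSQI of excluded minus retained participants. The shift in the treatment-minus-control difference is

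−m_T × g_T + m_C × g_C.

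The documents give no g; 3 points is assumed for illustration. A negative shift favours needling.

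| Excluded T / C | g_T / g_C | Shift (points) |
|---|---|---|
| 10% / 10% | 3 / 3 | 0 |
| 10% / 10% | 3 / 0 | −0.30 |
| 10% / 10% | 0 / 3 | +0.30 |
| 15% / 5% | 3 / 3 | −0.30 |
| 5% / 15% | 3 / 3 | +0.30 |
| 10% / 10% | 3 / −3 | −0.60 |
| 10% / 10% | −3 / 3 | +0.60 |

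**3. An upper bound.** Removing the worst fraction q of one arm, with nothing lost from the other, shifts that arm's mean by φ(z) / (1 − q) SD, where z is the 1 − q normal quantile. This gives 0.109 SD at 5%, 0.195 SD at 10% and 0.274 SD at 15%. With 56 per arm, a t test has 90% power for 0.618 SD, so the 10% bound is 0.195 / 0.618, about a third of that difference. It is an extreme case, not an expectation.

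**4. A milder mechanism, by simulation.** Assumptions, none from the documents: no true effect, SD 3, PSQI correlations of 0.5 with baseline and 0.7 between week 4 and week 8, and a logistic chance of loss that rises with week-4 PSQI (slope per SD). Loss is in one arm only except in the last row.

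| Loss | Slope | Week-8 bias under exclusion (points, absolute) |
|---|---|---|
| 10% | 0.5 | 0.11 |
| 10% | 1 | 0.19 |
| 13% | 1 | 0.25 |
| 20% | 2 | 0.55 |
| about 22% | 2 | about 0.60 |
| 19% against 5% | – | 0.35 |

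For scale, 0.618 × 3 is about 1.85 points. The 10% rows are 6% and 10% of that (0.11 / 1.85 and 0.19 / 1.85); the range 0.25 to 0.60 is 14% to 32%.

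**5. How far modelling helps.** If week-4 PSQI is observed for everyone and only week 8 is lost, a model using baseline and week-4 scores removes nearly all of this bias, because the cause of loss is then in the model. If the same participants lose week 4 as well, only baseline is left to adjust for:

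| Visit, loss | Exclusion | Baseline-adjusted | Remaining |
|---|---|---|---|
| Week 4, 13% | 0.35 | 0.27 | 77% |
| Week 4, 20% | 0.77 | 0.59 | 77% |
| Week 8, 13% | 0.25 | 0.17 | 68% |
| Week 8, 20% | 0.55 | 0.37 | 67% |

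Between two thirds and three quarters or so of the bias then remains.

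**The case against.** The best defence is that the rule can be read plainly: a case without an outcome measurement is left out, which is a complete-case analysis and what the stated t test would do anyway. Blinded statisticians and assessors limit exclusion made with knowledge of the arm. The article reports no arm-specific dropout, and the payment on completing all procedures encourages retention in both arms. Details of missing-data handling could sit in an analysis plan that is not shown.

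Much of this is fair, but the point survives. Complete-case analysis is biased under the same conditions, and blinding the analyst does not stop participants leaving for reasons tied to their arm. The exclusion is not a detail left open; the protocol itself fixes it.

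Four stronger readings are tempting and should not be made:
- **That completing a blank contradicts "Study medical records and CRFs are original records and cannot be altered" (Quality Control).** This can mean that entries are not overwritten, and the same paragraph asks the investigator to fill in every case truthfully. The missing-data paragraph reads as a sequence, with an unclear boundary between its last steps.
- **That failed measurements coded NM escape missing-data handling.** "This ensures a clear distinction from missing values" separates a code from a blank field at data entry; nothing is said about analysis.
- **That loss will differ by arm and response.** The documents make this plausible and no more.
- **That a mixed model would leave no bias.** Step 5 shows this depends on week-4 PSQI being observed. Loss caused by the burden of sessions would tend to fall before that visit.

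**Conclusion.** The point holds. The protocol states a rule under which randomised participants can be excluded on post-randomisation data, in undefined terms, and nothing else in the article restrains it. It bears on the primary comparison and should be replaced before analysis.

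The bias can go either way and is zero if exclusions are uninformative or balance across arms. The documents do not allow its size or sign to be computed. Under the assumptions of step 4 it is about 0.1 to 0.2 PSQI points at 10% loss in one arm (slopes 0.5 to 1) and 0.25 to 0.6 points at 13 to 22% loss (slopes 1 to 2). A steeper dependence on response would give more and a flatter one less. These figures show that the effect need not be negligible; they do not predict it for this trial.

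**What to change.** Delete the exclusion rule in Data Collection and Management and put in its place, for example:

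*All randomised participants are analysed in the group to which they were assigned, and none is excluded because an outcome value is missing. Blank fields are completed only from a source record; no value is invented. Missing PSQI scores, including those coded NM, are handled by a prespecified method that uses all collected PSQI data.*

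The method may be multiple imputation or a likelihood-based mixed model. If a mixed model is used, it should keep participants who have only a baseline score, for instance by placing baseline in the response vector. A standard model with baseline as a covariate would drop them and so break the first sentence.

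Add a delta or tipping-point sensitivity analysis, because loss before week 4 may not be missing at random. It will not remove such bias, but it shows how large a departure would change the conclusion.

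The cost is wording and a little more analysis work. No new data are needed, since PSQI is already scheduled at three visits. The Results section reports 120 of 124 participants enrolled by April 2025, so the change should be dated and made before anyone analysing the data sees the allocation.

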### Quality Control

All participants, including acupuncturists, evaluators, and statisticians, will be required to undergo training to ensure the quality of the studies. By formulating detailed and operable clinical trial specifications, the intervention will be based on careful adherence to the standard operating procedures.

All participants, including acupuncturists, evaluators, and statisticians, need to be trained to ensure the consistency of relevant data collection and the quality of research through the development of detailed and operational clinical trial protocols. The intervention will be based on careful adherence to standard operating procedures, and the acupuncturists will perform standardized shallow needling procedures according to the standard acupoint positioning. After the training, the assessment effects of the scale by outcome evaluators need to be checked for consistency, mainly including the same case being scored by independent examination by several outcome evaluators and the same case being scored multiple times by one evaluator to ensure consistency of the scores.

The investigator will fill in all cases truthfully and carefully according to the design requirements of the CRF. Study medical records and CRFs are original records and cannot be altered.

Laboratory data in clinical trials should be documented, and the original report or photocopy needs to be glued to the CRF.

In order to effectively improve the compliance of the participants, during the case screening and enrollment stage, it is necessary to maintain a patient and careful attitude; fully explain the purpose, process, and significance of the study to the participants; and ensure that the participants clearly understand the relevant content. At the same time, the participants will be clearly informed to strictly follow the established requirements to ensure the smooth progress of the study and the accuracy of the data.

## Results

Participant recruitment is currently underway. The first participant was enrolled in August 2023, marking the official commencement of the experiment. As of April 2025, a total of 120 participants have been enrolled in this clinical trial. The final results of the study are expected to be prepared and submitted for publication in January 2026.

## Discussion

This study is a randomized controlled clinical trial aimed at evaluating the clinical efficacy of shallow needling in the treatment of chronic PI and to further explore its underlying mechanism. The objectives include exploring a cost-effective, efficient, and safe standard therapy for chronic PI, as well as providing a scientific foundation for the clinical application and promotion of shallow needling therapy.

Through systematic data mining of extensive literature, we demonstrated that acupuncture points such as Shangen, Zhenjing, and Ezhong have been widely recognized for their efficacy in treating insomnia through shallow needling [33]. These acupoints correspond to the anatomical structures above the paranasal sinuses, where vibratory stimulation through shallow needling may induce resonance within the subcutaneous cavities. This resonant effect could further stimulate the Circle of Willis, thereby improving cerebral function and blood circulation [20]. A preliminary study indicates [34] that [name] frequently selected these acupoints in clinical practice, documenting significant improvement in over 80 patients with insomnia, many of whom experienced sleep onset during treatment. Furthermore, electroencephalography findings from the same study indicated that shallow needling can induce delta waves through regular and continuous vibratory stimulation. This mechanism shares similarities with the principle applied by hypnotists, who induce delta waves to treat insomnia specifically via the visual stimulation of a rhythmically swaying crystal ball. Our study will use these well-documented acupoints to improve therapeutic outcomes.

This trial will comprehensively assess the efficacy of shallow needling through both subjective and objective measures, including the PSQI, Hamilton Anxiety Scale, Insomnia Severity Index, and objective sleep monitoring via polysomnography. This multifaceted evaluation approach allows for a robust assessment of the treatment effects from various perspectives. Although previous studies have predominantly examined short-term outcomes, our study design incorporates a 4-week intervention period followed by a 4-week follow-up phase, enabling the investigation of both the immediate and sustained effects of shallow needling. This longitudinal design provides valuable insights into the therapeutic potential of the intervention. Additionally, to further elucidate the underlying neurophysiological mechanisms, we will analyze serum neurotransmitter levels and conduct thalamic MRS, exploring how shallow needling may modulate the neural pathways involved in sleep regulation. Moreover, this trial avoids the use of skin-penetrating interventions, ensuring participant safety and enhancing both participant compliance and the feasibility of the study.

Although our study comprehensively evaluates the efficacy of shallow needling for chronic PI, there are several limitations to consider. First, due to funding constraints, this study was designed as a single-center trial with a relatively limited sample size, which may, to some extent, affect the generalizability of the findings. Moreover, the assumed between-group difference used in the sample size calculation may have been overly optimistic, resulting in insufficient statistical power to detect more subtle yet clinically meaningful effects of shallow needling. Nevertheless, our study offers a valuable foundation for understanding the efficacy of shallow needling, and we hope that future large-scale, multicenter studies will further validate and extend these findings, thereby strengthening the evidence base for this intervention. Second, all participants received baseline pharmacotherapy with eszopiclone for ethical and adherence reasons, which may introduce confounding effects when interpreting the specific contribution of shallow needling. Therefore, we incorporated a follow-up period to reduce the residual pharmacological effects and more accurately assess the long-term efficacy attributable to shallow needling therapy. Finally, given the unique characteristics of shallow needling, developing a sham intervention that is both physiologically inert and indistinguishable from the actual treatment is difficult. Any form of simulated contact or scraping may inadvertently induce physiological reactions, thereby compromising its validity as a true placebo. Therefore, we adopted multidimensional objective outcome measures and blinded the evaluators and statisticians to reduce potential bias risks. At the same time, a 4-week follow-up was conducted to reduce the short-term placebo effect and enhance the validity of the research results. We hope that future research can develop and apply innovative sham-control methods tailored to shallow needling techniques to further reduce the possible placebo bias.

To the best of our knowledge, this is the first randomized controlled trial to objectively assess the efficacy of shallow needling for the treatment of insomnia and provide new insights into its neurophysiological mechanisms. The results of this study will establish a basis for the wider use of shallow needling in clinical practice and provide fresh evidence-based support for its application in treating insomnia.
